### Study setting and population

Rio de Janeiro and Niterói cities are located in the State of Rio de Janeiro, Brazil. Niterói has an area of 134 km
^2^ and a population of 484,918 in 2010. Rio de Janeiro is the second largest city in Brazil with 6,320,446 inhabitants in 2010 and an area of 1,200 km
^2^. The two cities sit on opposite sides of the Guanabara Bay and are linked by a long bridge, which transports a large commuter population between Niterói and Rio de Janeiro.

The cities are divided into health districts, for the purpose of planning and delivering care - ten in Rio de Janeiro and seven in Niterói. In Rio de Janeiro,
*Wolbachia* deployments will be conducted in one of the administrative areas of the city (
Figure 1; produced in ArcMap version 10.5, ESRI, CA), in an area of approximately 90 km
^2^ and with 886,551 inhabitants, 39% of whom live in slums. The total release area in Niterói is approximately 83 km
^2^ covering a population of 373,117 (
Table 1). For the purposes of
*Wolbachia* deployment, the Rio de Janeiro and Niterói intervention areas are each divided into 4 release zones, respectively, which are aligned with neighbourhood administrative boundaries.

**Figure 1. f1:**
[figure not shown]
Map of (
**a**) Rio de Janeiro and (
**b**) Niterói
*Wolbachia-*treated and untreated areas (produced in ArcMap version 10.5, ESRI, CA).

**Table 1. T1:** Demographic characteristics of
*Wolbachia* treated and untreated areas, Niterói and Rio de Janeiro (source: 2010 Brazil population census). Neighbourhoods Population Area (Km
^2^) Population density

	Neighbourhoods	Population	Area (Km ^2^)	Population density
Niterói				
Release Zone 1	4	23,747	9.2	2,581
Release Zone 2	11	68,695	50.6	1,357
Release Zone 3	13	178,891	12.6	14,197
Release Zone 4	5	101,784	10.8	9,424
Non-release control area	19	111,801	51.2	2,183
Total	52	484,918	134.4	3,608
Rio de Janeiro				
Release Zone 1	10	107,130	11.8	9,078
Release Zone 2	6	150,646	33.5	4,496
Release Zone 3.1	8	408,036	28.2	14,469
Release Zone 3.2	4	220,739	12.0	18,394
Non-release control area	51	1,512,608	117.3	12,895
Rest of city (no releases)	79	3,921,287	996.5	3,935
Total	158	6,320,446	1,199.3	5,270

In Rio de Janeiro, two administrative areas adjacent to the release area have been designated
*a priori* as a comparative control zone (
Figure 1), based on synchronous historical dengue and chikungunya time series (
Figure 2 and
Figure 3). In Niterói, the remaining untreated area of the city has been designated as the comparative control zone (
Figure 1).

**Figure 2. f2:**
[figure not shown]
Dengue incidence in
*Wolbachia-*treated vs untreated areas of (
**a**) Rio de Janeiro (2000–2017) and (
**b**) Niterói (2007–2017) (source: Brazilian National Disease Surveillance System (SINAN)).

**Figure 3. f3:**
[figure not shown]
Chikungunya incidence in
*Wolbachia*-treated vs untreated areas of (
**a**) Rio de Janeiro (2015–2017) and (
**b**) Niterói (2015–2017) (source: Brazilian National Disease Surveillance System (SINAN)).

### Wolbachia release and monitoring

Staged
*w*Mel
*Wolbachia*-mosquito deployments will be implemented in Niterói and Rio de Janeiro, in order to achieve
*Wolbachia* establishment across the two cities. Pilot releases commenced in late 2015, and city-wide deployments are ongoing through to the end of 2019.
*Wolbachia*-containing adult mosquitoes will be released at one location per 50 x 50 meter grid square for a minimum of 16 consecutive weeks in each release zone. In areas where
*Wolbachia* frequency remains low after 16 weeks of releases, or where particularly high wild type
*Ae. aegypti* populations are observed,
*Wolbachia*-containing mosquito eggs will also be released to complement adult releases with the aim of accelerating
*Wolbachia* establishment. Monitoring of
*Wolbachia* frequency will be done using BG-Sentinel mosquito traps (BioGents, Germany), distributed throughout the release area at a density of 16 traps per km
^2^. Traps will be serviced weekly and all collected mosquitoes identified morphologically by microscopy. From eight weeks after the start of releases, a maximum of 10
*Ae. aegypti* (male and female) per trap will be tested individually for
*Wolbachia* using quantitative polymerase chain reaction (qPCR).
*Wolbachia* screening will be performed biweekly during releases and until establishment, then every 1–3 months thereafter. All surplus
*Ae. aegypti* will be biobanked. Mosquito collection and screening results will be stored in a custom designed web-based data repository. The
*Wolbachia* prevalence in screened
*Ae. aegypti* will be reported aggregated to each release zone, calculated as the total number of
*Ae. aegypti* mosquitoes that tested positive for
*Wolbachia* aggregated across all BG traps in the zone, divided by the total number of
*Ae. aegypti* that were screened in that zone.

### Epidemiological data sources

The two proposed strategies for the evaluation of the impact of large-scale
*Wolbachia* deployments on arboviral disease incidence in Niterói and Rio de Janeiro make use of existing data on dengue, chikungunya and Zika case notifications to the Brazilian national disease surveillance system (SINAN). Dengue surveillance has been in place since its re-emergence in 1986 and data is available from the SINAN system since 2000. Zika and chikungunya became notifiable diseases in 2015.

Suspected cases of dengue and other arboviral diseases are required to be reported to the city health department
^25^, according to a case definition of fever plus two other symptoms including malaise, headache, myalgia, nausea, vomiting, cutaneous rash, and arthralgia. Dengue case notifications include an indication of disease severity (dengue, dengue with alarm signals, severe dengue, fatal dengue). A variable proportion of notified suspected cases are tested by IgM serology or PCR, following the Brazilian guidelines
^26^ and the timing between onset of symptoms and blood collection. The number of cases in a given period of time may limit the availability of tests, and PCR testing is routinely performed only for severe and fatal cases, pregnant women and young children
^26^. In 2016, 4.8% of notified dengue cases in Rio de Janeiro and 11.5% in Niterói were supported by a positive IgM serology result, and only 0.2% of notified cases in Rio and 0.03% in Niterói had a positive PCR result. The ability to confirm dengue cases by serology is impaired since the Zika outbreak due to serological cross-reactivity between the dengue and Zika viruses. As PCR testing is performed only in certain patient populations, the proportion positive is unlikely to be generalisable to all notified cases. Therefore, for the purpose of our analyses we will use all notified dengue cases (suspected and laboratory-confirmed) as the primary endpoint.

In the absence of a reliable serological test that does not cross-react with dengue, Zika lab diagnosis is done solely on the basis of molecular detection (real-time PCR) up to the first 5 days in serum and 15 days in urine. This has severely limited the ability to confirm Zika virus infection among notified cases (3.5% in 2016, 19.3% in 2017).

Chikungunya diagnoses can be confirmed either through PCR or serology, as it does not cross-react with Zika or dengue. The proportion of notified cases with supportive laboratory findings is higher than for dengue: 31.9% and 18.2% in Rio and Niterói, respectively, in 2016.

Anonymized disaggregate (line-listed) data on notified suspected and laboratory-confirmed dengue, chikungunya and Zika cases will be extracted from the SINAN system for the historical pre-intervention period (2000–2016 for dengue, and 2015–2016 for chikungunya and Zika) and the prospective post-intervention period (2017–2023). The dataset will include age, sex, neighbourhood of primary residence, date of illness onset, date of notification, reporting health clinic, disease severity, hospitalisation, death, and where available, geocoordinates of primary residence, type of diagnostic test performed, diagnostic test result, and final diagnostic classification. Population data from the Brazilian census (IBGE) and population by neighbourhood of residence obtained from the cities of Rio and Niterói will be used to estimate the population in each release zone. The incidence rate (number of new dengue, Zika or chikungunya cases divided by the population at risk) will be expressed per 100,000 inhabitants.

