### Controlled interrupted time series analysis

Interrupted time series (ITS) analysis is a valuable study design for evaluating the effectiveness of a population-level health intervention that is implemented at a clearly defined point in time
^27^. It uses a set of historical observations of an outcome of interest (in this context monthly dengue case notifications) to establish an underlying trend, which is assumed to be ‘interrupted’ by the introduction of an intervention (in this case
*Wolbachia* releases). Comparison of the trend in monthly case notifications in the post-intervention period with the hypothetical scenario of no intervention (the ‘counterfactual’, inferred from the historical time series and the untreated control area), provides an estimate of the intervention effect. Segmented regression will be used to estimate the effect of
*Wolbachia* releases on monthly case counts of dengue and chikungunya, using an appropriately defined model: e.g. negative binomial regression for autocorrelated count data with population offset, adjusted for temporal effects using indicator variables or flexible cubic splines, and assuming a step change post-intervention. The
*Wolbachia* intervention effect will be estimated from the interaction between a binary ‘area’ variable (intervention vs control area) and a binary ‘period’ variable (post
*-*intervention
** vs
** pre
*-*intervention). The post-intervention period will be defined for the control area beginning at the same time as the post-intervention period in the comparative release zone. This allows explicitly for a level change in the outcome (dengue case incidence) in both intervention and control areas in the post-intervention period, for example in a scenario where other secular events coincident with the
*Wolbachia* deployments may have influenced dengue incidence in both intervention and control areas independent of
*Wolbachia*. An additional analysis will consider
*Wolbachia* frequency as a continuous covariate or categorised into quintiles of exposure reflecting the measured

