*Wolbachia* release dengue case numbers in the treated zones were drawn from the same model-generated distribution, modified by an additional parameter for an intervention effect of Relative Risks = 0.6, 0.5, 0.4, 0.3. For each of these four ‘true’ effect sizes and a null effect (RR = 1), applied to each of the 1000 simulated time series, the ‘observed’ effect size was calculated from a negative binomial regression model of monthly case counts in the treated and untreated zones, as described above. Post-intervention time periods of 1, 2 or 3 years were simulated, with the pre-intervention period fixed at 7 years. The estimated power to detect a given effect size was determined as the proportion of the 1000 simulated scenarios in which a significant intervention effect (p<0.05) was observed. These simulations indicate 80% power to detect a reduction in dengue incidence of 50% or greater after three years of post-intervention observations, and a reduction of 60% or greater after two years.

The primary endpoint for the ITS analysis will be dengue cases notified to the disease surveillance system. The secondary endpoints will be: a) the count of severe dengue cases reported to the surveillance system, b) the count of fatal dengue cases reported to the surveillance system, and c) chikungunya and Zika cases notified to the disease surveillance system.

Although the historical time series for chikungunya and Zika incidence is short, we will nonetheless describe the incidence during and after
*Wolbachia* deployments relative to the
*a priori* defined non-release control areas for both Niterói and Rio de Janeiro.

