^2^, with population >1 million). We also cannot exclude the possibility of a concurrent change in socio-demographic or ecological factors related to dengue risk, or a change in dengue control practices, between the intervention and control areas independent of the
*Wolbachia* intervention, but given the strong synchrony in dengue incidence between intervention and control zones for over a decade prior to releases this is considered unlikely. 

Human mobility also presents a potential challenge to this study, especially during the period in which staged releases are occurring and
*Wolbachia* levels are heterogeneous, as individuals are likely to spend time in both
*Wolbachia*-treated and untreated areas, making it difficult to determine the place of illness acquisition among notified cases of arboviral disease. Travel between areas means that the true
*Wolbachia* exposure status of individuals resident in
*Wolbachia*-treated and untreated areas becomes more similar, thereby diluting the observed intervention effect towards the null.

The introduction of Zika and chikungunya viruses brought new challenges to health surveillance and a greater willingness for better vector control in affected regions. With the re-emergence of yellow fever in Brazil
^8^, there is even more potential public health benefit if the
*Wolbachia* intervention successfully reduces the vector competence of
*Ae. aegypti* mosquitoes in the field and reduces arboviral disease incidence. No specific treatment for dengue, chikungunya or Zika currently exists. Although a vaccine against dengue (Sanofi Dengvaxia
^®^) was licensed in 2015, it was recently found to enhance the severity of subsequent dengue infection in individuals who were seronegative at the time of vaccination. As a result, a serology test prior to the administration of the vaccine is required to confirm previous dengue infection, increasing costs and decreasing feasibility in high-burden areas
^34^.

Releases of
*Wolbachia* are completed or underway in eight countries, with no evidence of local transmission of dengue, Zika or chikungunya in places where
*Wolbachia* is established at high levels
^21^. The implementation of the

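### The step-change estimator has no area-specific trend and no stated check of a constant pre-release ratio, so any steady divergence between treated and control areas would enter the Wolbachia rate ratio

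*Protocol article*

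**What the plan says.** All references are to the protocol article.

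- **Controlled interrupted time series analysis.** The history is meant to supply an underlying trend that the releases interrupt. The model is introduced as an example, "using an appropriately defined model: e.g. negative binomial regression for autocorrelated count data with population offset", with time "adjusted for temporal effects using indicator variables or flexible cubic splines" and "assuming a step change post-intervention". The effect sentence carries no such qualifier: the "intervention effect will be estimated from the interaction between a binary" area variable and a binary period variable. No area by time term is mentioned. Each release zone, and each city's aggregate release area, is compared with that city's control area, yearly and cumulatively for five years.
- **Epidemiological data sources.** Line-listed data will be extracted for the "historical pre-intervention period (2000–2016 for dengue") and for 2017–2023 afterwards.
- **Power paragraph.** The simulation distribution was fitted to 2007–2016, "with the pre-intervention period fixed at 7 years" and one to three years after release.
- **Discussion.** Differential change in socio-demographic or ecological factors, or in control practices, is admitted as possible but judged unlikely "given the strong synchrony in dengue incidence between intervention and control zones for over a decade prior to releases".

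**The concern.** Allocation was not randomised, so the estimate rests on one assumption: without releases, the treated:control incidence ratio after release would have equalled its pre-release value. The area by period interaction removes a fixed difference between areas and any shock common to both. It does not remove a gradual relative change, for instance in reporting coverage or urban conditions. Such a change moves the point estimate itself, so robust standard errors do not help.

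Synchrony is a statement about timing. Two series can peak in the same months while the ratio of their levels drifts. The document states no check of that ratio, although the data needed are already to be extracted.

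At stake is the rate ratio itself. It could show an effect that is not there, or hide or exaggerate a real one. Because the analysis is cumulative over five years, the standard error shrinks while the distance between the two windows grows.

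**Working it through.** **1. The plan's own power figures.** The negative binomial dispersion k and the monthly means are not given, so the simulation cannot be rerun. A consistency check uses Var(log RR) = 2k(1/n_pre + 1/n_post), in months, with n_pre = 84, two-sided 0.05 and independent months (assumed).

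- Three years (n_post = 36): 80% power is reached at RR 0.5 but not at RR 0.6 if k lies between 0.419 and 0.771.
- Two years (n_post = 24): 80% power is reached at RR 0.4 but not at RR 0.5 if k lies between 0.571 and 0.998.

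Both statements hold for k from 0.57 to 0.77, so they agree with each other. I use k = 0.67 below.

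**2. Bias of the step-only model.** If the log treated:control ratio falls by δ per year and the true RR is 1, the interaction is approximately the mean log ratio after release minus the mean before. The apparent RR is therefore exp(−δ × gap), where gap is the distance between window midpoints. Two post-release windows bracket the plan:

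- (a) three years directly after the baseline (2017–2019, midpoint 2018.5);
- (b) 2020–2021 (midpoint 2021.0), since releases end in 2019 and reporting is planned two years later.

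Baseline midpoints are 2008.5 (2000–2016) and 2012.0 (2007–2016). The drift rates are assumptions; the document gives none.

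| Baseline | Window | Gap (years) | 1%/yr | 2%/yr | 3%/yr |
|---|---|---|---|---|---|
| 17 years | (a) | 10.0 | 0.90 | 0.82 | 0.74 |
| 17 years | (b) | 12.5 | 0.88 | 0.78 | 0.69 |
| 10 years | (a) | 6.5 | 0.94 | 0.88 | 0.82 |
| 10 years | (b) | 9.0 | 0.91 | 0.84 | 0.76 |
| 7 years | (a) | 5.0 | 0.95 | 0.90 | 0.86 |

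Drift in the other direction gives the reciprocals. At 2% with a gap of 10 years, a true RR of 0.5 would appear as 0.5 × 0.82 = 0.41 or 0.5 / 0.82 = 0.61.

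**3. False-positive rate at 2% per year, window (a).** SE = √[2 × 0.67 × (1/n_pre + 1/36)] gives 0.209, 0.220 and 0.231 for 204, 120 and 84 pre-release months. With bias δ × gap of 0.20, 0.13 and 0.10, the two-sided rejection rate is about 16%, 9% and 7%. A simulation of 300 series per scenario gave 16%, 13% and 10%, against 5%, 8% and 7% with no drift (Monte Carlo error 1 to 3 points). It ignores autocorrelation.

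**4. Adding an area by linear-time term.** In the same simulations at 2% drift, the mean estimate returned to 0.99, 0.99 and 1.02. The cost in precision with three post-release years is:

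| Pre-release years | SE ratio | Power at RR 0.5, without → with the term |
|---|---|---|
| 17 | 1.27 | 91% → 74% |
| 10 | 1.46 | 88% → 58% |
| 7 | 1.64 | 85% → 45% |

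**5. What the pre-release slope can show.** SE(slope) = √[2k / Σ(t − t̄)²], with t in years, so Σ(t − t̄)² = n(n² − 1)/(12 × 144). This gives 0.017, 0.037 and 0.063 per year for 204, 120 and 84 months. The 95% half-widths (1.96 × SE) are about 3, 7 and 12 percentage points per year. A non-significant slope therefore does not establish a constant ratio, which is why the interval must be shown.

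**The case against.** The other side has real substance.

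- **Extraction range.** 2000–2016 is the period for which data are drawn. A reader might infer that the effect is measured against one 17-year average, but the document does not say so, and the contrast is control-adjusted with flexible time terms.
- **Windows.** A reader might infer that the 17-, 10- and 7-year periods contradict each other. They describe an extraction range, the series behind the simulation and the simulated layout, and seven plus three years may simply split the ten-year series. What stands is only that no regression baseline is named.
- **Matching.** The analysis section also calls the controls well matched on demographics and on historical incidence, which concerns levels as well as timing. The supporting figures are not visible here, so nothing shows that the ratio did drift. But matching on average does not show a flat ratio, and in Niterói Table 1 gives a control density of 2,183 per km² against 14,197 and 9,424 in Zones 3 and 4, which hold (178,891 + 101,784)/373,117 = 75% of the treated population.
- **Population change.** The population offset largely handles it, provided the figures are kept current.
- **Room for more.** The model is given as an example, and an analysis plan not shown may add a trend term. The outbreak signals use a five-year history within each area, and a further analysis uses measured Wolbachia frequency. These complement the primary estimate, but none is described as a test of its assumption.

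**Conclusion.** The point holds in conditional form. The stated estimator assumes a constant treated:control ratio, the Discussion concedes that this could fail, and no check is stated. If the areas diverge steadily, the divergence enters the rate ratio in full, in either direction, and more so the longer the baseline. At an assumed 2% per year, a true RR of 1 becomes 0.78 to 0.82 with 17 years and 0.84 to 0.88 with 10.

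This rests on assumed drift rates, a log-linear drift, independent months, and k = 0.67 for the error rates. The size and sign of any real drift are unknown, so the document does not support saying that drift is being reported as a Wolbachia effect. Nor does it show that 2007–2016 has to be the primary baseline: shortening from 17 to 10 years leaves most of the bias in place (0.84 instead of 0.78 in window (b)), and the longer history measures the pre-release slope far better. This is an inexpensive improvement, not a fatal flaw.

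**What to change.** 1. Keep the area by period step-change model as primary.
2. For each comparison (each zone and each city aggregate against its control area), report the fitted pre-release slope of the treated:control incidence ratio with its 95% confidence interval. Do not treat non-significance as proof of a constant ratio.
3. Pre-specify the same model with an area by linear calendar-time term as a sensitivity analysis, shown beside the primary estimate.
4. State which years form the regression baseline in each city. An alternative start year can be a second sensitivity analysis.

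**Cost.** Some wording and one extra model per comparison, on data already to be extracted. The trend-adjusted standard error is about 1.3 to 1.6 times larger with three post-release years, so that model is not suitable as primary and its loss of significance alone should not be read as absence of effect. It corrects only a linear drift.

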### Controlled interrupted time series analysis

Interrupted time series (ITS) analysis is a valuable study design for evaluating the effectiveness of a population-level health intervention that is implemented at a clearly defined point in time
^27^. It uses a set of historical observations of an outcome of interest (in this context monthly dengue case notifications) to establish an underlying trend, which is assumed to be ‘interrupted’ by the introduction of an intervention (in this case
*Wolbachia* releases). Comparison of the trend in monthly case notifications in the post-intervention period with the hypothetical scenario of no intervention (the ‘counterfactual’, inferred from the historical time series and the untreated control area), provides an estimate of the intervention effect. Segmented regression will be used to estimate the effect of
*Wolbachia* releases on monthly case counts of dengue and chikungunya, using an appropriately defined model: e.g. negative binomial regression for autocorrelated count data with population offset, adjusted for temporal effects using indicator variables or flexible cubic splines, and assuming a step change post-intervention. The
*Wolbachia* intervention effect will be estimated from the interaction between a binary ‘area’ variable (intervention vs control area) and a binary ‘period’ variable (post
*-*intervention
** vs
** pre
*-*intervention). The post-intervention period will be defined for the control area beginning at the same time as the post-intervention period in the comparative release zone. This allows explicitly for a level change in the outcome (dengue case incidence) in both intervention and control areas in the post-intervention period, for example in a scenario where other secular events coincident with the
*Wolbachia* deployments may have influenced dengue incidence in both intervention and control areas independent of
*Wolbachia*. An additional analysis will consider
*Wolbachia* frequency as a continuous covariate or categorised into quintiles of exposure reflecting the measured
*Wolbachia* prevalence in the local mosquito population. The outcome distribution is assumed to be negative binomial to allow for overdispersion. Robust standard errors will be used to account for autocorrelation and heteroskedasticity. If an excess of zero counts is apparent, the proposed negative binomial model will be nested within a zero-inflated negative binomial model of the same structure. A likelihood ratio test can be performed to test model fit.

Separate analyses will be performed for each release zone compared with its pre-defined control area, and for the aggregate release areas in each city compared with the control area for each city. The availability of comparative control areas – well-matched to the release area in demographic characteristics and historical arboviral disease incidence (
Figure 2 and
Figure 3) – permits a robust, controlled analysis in which the confounding effects of seasonality and inter-annual variability can be adjusted for. The intervention effect will be estimated after 12 months of post-release observations have accumulated, and each 12 months thereafter for five years using cumulative post-release observations, for each release zone individually and in aggregate for each city.

Power was estimated for the ITS analysis using 1000 simulated datasets drawn from a negative binomial distribution fitted to a ten-year time series (2007–2016) prior to
*Wolbachia* deployment, of monthly dengue case notifications from release and control zones in Niterói and Rio de Janeiro. The simulated time series of dengue case numbers in the control zones as well as the pre-
*Wolbachia* release dengue case numbers in the treated zones were drawn directly from this model-generated distribution. Post-
*Wolbachia* release dengue case numbers in the treated zones were drawn from the same model-generated distribution, modified by an additional parameter for an intervention effect of Relative Risks = 0.6, 0.5, 0.4, 0.3. For each of these four ‘true’ effect sizes and a null effect (RR = 1), applied to each of the 1000 simulated time series, the ‘observed’ effect size was calculated from a negative binomial regression model of monthly case counts in the treated and untreated zones, as described above. Post-intervention time periods of 1, 2 or 3 years were simulated, with the pre-intervention period fixed at 7 years. The estimated power to detect a given effect size was determined as the proportion of the 1000 simulated scenarios in which a significant intervention effect (p<0.05) was observed. These simulations indicate 80% power to detect a reduction in dengue incidence of 50% or greater after three years of post-intervention observations, and a reduction of 60% or greater after two years.

The primary endpoint for the ITS analysis will be dengue cases notified to the disease surveillance system. The secondary endpoints will be: a) the count of severe dengue cases reported to the surveillance system, b) the count of fatal dengue cases reported to the surveillance system, and c) chikungunya and Zika cases notified to the disease surveillance system.

Although the historical time series for chikungunya and Zika incidence is short, we will nonetheless describe the incidence during and after
*Wolbachia* deployments relative to the
*a priori* defined non-release control areas for both Niterói and Rio de Janeiro.

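### The city-aggregate analysis applies one binary pre/post step to four zones released in stages, and no start date for that step is fixed; the aggregate RR may be diluted, depending on the date chosen

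*Protocol article*

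**What the plan says.** All places are in the Protocol article.

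- **Model** (Controlled interrupted time series analysis). The regression is described as "adjusted for temporal effects using indicator variables or flexible cubic splines, and assuming a step change post-intervention", with the effect estimated "from the interaction between a binary ‘area’ variable (intervention vs control area) and a binary ‘period’ variable". The section introduces the design as suited to an intervention "implemented at a clearly defined point in time".
- **Start rule** (same section). "The post-intervention period will be defined for the control area beginning at the same time as the post-intervention period in the comparative release zone".
- **Scope** (same section). Analyses are planned for each zone and also "for the aggregate release areas in each city compared with the control area for each city". Both are to be updated every 12 months for five years on cumulative post-release data.
- **Staging** (Wolbachia release and monitoring). "Pilot releases commenced in late 2015, and city-wide deployments are ongoing through to the end of 2019". No zone dates are given.
- **Other anchors.** Study design counts five years from Wolbachia establishment. Epidemiological data sources labels 2000–2016 as pre-intervention for dengue and 2017–2023 as post-intervention. Dissemination of study results reports two years after releases are complete.
- **Chikungunya and Zika.** Objective 1 estimates a reduction in both. The time series section names dengue and chikungunya for segmented regression and lists both chikungunya and Zika as secondary endpoints. It then says: "Although the historical time series for chikungunya and Zika incidence is short, we will nonetheless describe the incidence during and after".

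**The concern.** A single step suits one zone with one start date. A series summed over four zones that start at different times has no single interruption. An early step counts untreated zones as treated; a late step leaves treated zones in the pre-period. Both errors pull the aggregate RR towards 1, but by very different amounts. With the date not fixed in this document and several candidates available, the same data could give materially different city estimates, and the choice could be made after the data are seen.

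**Working it through.** **The plan's own figure.** The article gives no figure for the aggregate under staging. Its 80% power statements cannot be reproduced, because the fitted means and dispersion are not given. As described, the simulation applies the full RR to post-release counts and does not mention staging.

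**Inputs from Table 1.** Population shares, in zone order:
- Niterói (373,117): 6.4%, 18.4%, 47.9%, 27.3%. Zones 3 and 4 hold (178,891 + 101,784)/373,117 = 75.2%.
- Rio de Janeiro (886,551): 12.1%, 17.0%, 46.0%, 24.9%. Zones 3.1 and 3.2 hold (408,036 + 220,739)/886,551 = 70.9%.

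**Assumptions, not in the documents.** Zones are completed in numbered order, at months 6/16/26/36 (schedule A) or 12/18/30/36 (schedule B) after January 2017. Incidence is flat and equal across zones, the full effect is immediate, and the true RR is 0.50. End-2021 is month 60.

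**Formulas.** Let D be the population-weighted mean completion month.
- Step at month s, no later than the first zone: apparent RR = 1 − (1 − RR) × (60 − D)/(60 − s).
- Step at the last zone (month 36), with n pre-period months: apparent RR = RR / [1 − (1 − RR) × (36 − D)/n].
- Zone-specific starts: every post month carries RR and every pre month carries 1, so apparent RR = RR.

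**Worked case, Niterói, schedule A.** D = 0.0636×6 + 0.1841×16 + 0.4795×26 + 0.2728×36 = 25.6.
- Step at January 2017: 1 − 0.5 × (60 − 25.6)/60 = 0.71.
- Step at the last zone, n = 84: (36 − 25.6)/84 = 0.124, and 0.5/(1 − 0.5 × 0.124) = 0.53.

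**Apparent RR at end-2021 for a true RR of 0.50**

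| City, schedule | D | Step Jan 2017 | Step first zone | Step last zone, n = 84 | Step last zone, n = 156 |
|---|---|---|---|---|---|
| Niterói, A | 25.6 | 0.71 | 0.68 | 0.53 | 0.52 |
| Niterói, B | 28.3 | 0.74 | 0.67 | 0.52 | 0.51 |
| Rio, A | 24.4 | 0.70 | 0.67 | 0.54 | 0.52 |
| Rio, B | 27.3 | 0.73 | 0.66 | 0.53 | 0.51 |

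Here n = 84 is the seven-year pre-period of the power simulation, and n = 156 is 2007–2019. Three other assumed schedules (6/12/18/24, 9/18/27/36 and 18/24/30/36) with a January 2017 step give 0.64–0.75 at end-2021 and 0.60–0.68 at end-2023.

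**Follow-up.** A step at the end of 2019 leaves January 2020 to December 2023, which is four years. Five yearly aggregate estimates by end-2023 need a start by January 2019, before the stated end of releases.

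**Pilots.** Suppose all of Zone 1 had the full effect for 14 pre-period months. In Rio with 84 pre months, 0.5/(1 − 0.5 × 0.1208 × 14/84) = 0.505. In Niterói with 120 pre months the result is 0.502. For dengue the overlap is negligible.

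**The case against.** The strongest reply is that no sentence assigns the aggregate a common date. The quoted start rule is zone-specific and is how the plan handles staging. Combining cumulative post-release data in aggregate could mean pooling zone-specific months. The model is offered as an example of an appropriate one, and the 2017–2023 split appears in a sentence about data extraction. The report two years after completion fits a last-zone step at least as well as a January 2017 step, and a last-zone step dilutes little. A journal article may also leave such coding to a fuller plan.

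Much of this stands: dilution is possible, not established, and the zone-level analyses are untouched by it. The reply does not remove the conflict. The article fixes a binary period for the effect, applies it to a staged aggregate, and states anchors that cannot all be time zero. The least-diluting single date also conflicts with its own five-year schedule if a city finishes at end-2019.

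The analysis by measured Wolbachia frequency addresses graded exposure and deserves credit, but it is an additional analysis. The Discussion acknowledges uneven Wolbachia levels during staging, but attributes dilution to human movement.

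A reader might infer more than the text supports:
- **The aggregate is the headline result.** Zone and aggregate estimates are planned together and neither is called primary.
- **Zones that fail to establish drop out.** No rule says so; establishment appears as the origin of the follow-up horizon.
- **Chikungunya and Zika will only be described.** The article does not say only; its statements on this differ and need reconciling.

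**Conclusion.** The point holds as an unresolved and conflicting definition of time zero for the city aggregates, joined to a model form that cannot represent staged release with any single date. It is not a demonstrated bias. For a true RR of 0.50, the aggregate at end-2021 could range from no dilution (zone-specific starts), through 0.51–0.54 (last-zone step), to 0.66–0.74 (January 2017 or first-zone step). These figures rest on assumed zone order and dates, flat and equal incidence, and an immediate full effect; the timing of epidemic years would shift them. The error is towards the null, so it would understate a benefit and not create one. Pilot overlap is immaterial for dengue.

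**What to change.** - Estimate each city's aggregate effect from a zone-by-month model with zone effects. Each zone's exposure switches on at its own prespecified date, tied to releases and not to observed establishment.
- Code that zone's roll-out months as a separate transition period, or exclude them.
- Enter the city's control series once, with calendar-month effects. If it is instead paired with each zone in turn, use standard errors that allow for its reuse.
- Reconcile Study design, Epidemiological data sources, Controlled interrupted time series analysis and Dissemination of study results to this time zero. Reconcile the five-year horizon with data ending in 2023 as well: zone-specific starts do not lengthen follow-up for a zone finishing at end-2019.
- For chikungunya and Zika, state consistently in objective 1, the regression description and the endpoint list whether an effect is estimated or incidence is described.

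The cost is a few transition months per zone and slightly more model code. The planned extract already holds neighbourhood of residence and date of illness onset, so no new data are needed.
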